## **4.4. Dose Limiting Toxicities**

Adverse events and other symptoms will be graded according to the NCI Common Terminology Criteria for Adverse Events version 3.0. (<http://ctep.cancer.gov/reporting/ctc.html>).

Dose-limiting toxicity (DLT) is defined as any of the following when considered related to CP-675,206 therapy:

1. • Any CTC Grade 4 treatment related toxicity of any duration.
2. • Other Grade 3 or greater toxicities that do not recover to ≤ Grade 1 or baseline within 7 days of maximal management
3. • Grade 2 or greater treatment related clinical autoimmune toxicity of critical organs, which are defined as lung, heart, kidney, bowel, bone marrow and nervous system, including the eye (except anterior uveitis).

Assessment of DLTs during the first 12 weeks after CP-675,206 dosing will be completed to determine the next dose level.

## **Maximum Tolerated Dose**

The MTD will be the maximum dose level of CP-675,206 administered (3, 6, 10 or 15 mg/kg) in combination with radiation, at which no subject experiences a life-threatening adverse event and at which 0/6 or 1/6 patients (<33%) experiences a DLT during the first 12 weeks following CP-675,206 dose administration.

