#### 2.3.2.1. Trial A3671001 - Safety

The most frequently observed treatment-emergent, all-causality AEs (in ≥10% of patients) were rash (29.5%), nausea (27.3%), diarrhea (27.3%), fatigue (25.0%), pruritus (22.7%), headache (18.2%), asthenia (13.6%), vomiting (13.6%), fever (11.4%), peripheral edema (11.4%), weight loss (11.4%), dizziness (11.4%), and anemia (11.4%). The incidence of rash, pruritus, and diarrhea appeared to increase with dose. Hyperthyroidism was possibly immune-mediated as evidenced by alteration in autoantibodies. Other possible immune-mediated events, such as skin hypopigmentation/vitiligo, psoriasis, hypophysitis, and alterations in pituitary activity, had no direct evidence of the mechanism of toxicity.

Treatment-emergent, treatment-related CTC Grade 3 events were limited to diarrhea (1 patient each at 6 and 10 mg/kg and 2 patients at 15 mg/kg), rash (1 patient at 15 mg/kg), enzymatic alteration (1 patient with elevated lipase at 10 mg/kg), and asthma (1 patient with pre-existing history at 10 mg/kg). Three CTC Grade 4 events were reported (respiratory arrest, respiratory failure, and malignant melanoma). In all cases, the cause for the CTC Grade 4 event was not the study drug.

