## **Dose Escalation Rules**

To minimize the risk of this combination to patients, dosing in the first dose level cohort only will proceed by evaluating safety in the first patient for 12 weeks after the dose of CP-675,206. Prior CP-675,206 single-agent data on safety findings from Pfizer studies indicate that a 6-week follow-up interval was appropriate. However, in order to monitor for potential late-onset toxicities due to the combination of CP-675,206 with radiation, this protocol will follow patients for 12 weeks.

Dosing will be conducted in subsequent dose level cohorts of at least 3 patients, with patients assigned to a dose group after verification by the Investigator of eligibility.

Safety considerations in a current dose level will be assessed as follows to determine dose level escalation:

**1.** If no patient experiences a DLT in the first 12 weeks, the trial will proceed to the next dose level cohort

**2.** If 1/3 patients experiences a DLT in the first 12 weeks, expand cohort to 3 additional patients, and then determine:

- 1. • If 1/6 patients experiences a DLT in the first 12 weeks, escalate to the next dose level.
  2. • If ≥2/6 patients experience a DLT in the first 12 weeks, the current dose level will be considered above the maximum tolerated dose and dose escalation will be discontinued.

**3.** If ≥2/3 patients experience a DLT in the first 12 weeks, the current dose level will be considered above the MTD and the preceding dose level cohort will be expanded to a minimum of 6 patients.

The dose escalation will end after DLT is observed in ≥2 out of 3-6 patients treated at any dose level or after 6 patients at the highest dose level defined (CP-675,206, 15 mg/kg) have completed the 12-week observation period.

Additional patients may be entered as needed at any dose level, including intermediate dose levels, to more fully elucidate the pattern of toxicity and/or better define the MTD.

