### **6.1.1. Dose Levels**

The starting dose of CP-675,206 will be 3.0 mg/kg, a dose shown to be safe as a single agent in previous trials. Dose escalation will only proceed to the 6, 10 and 15 mg/kg dose levels if adequate safety is demonstrated at the previous CP-675,206 dose level tested.

A minimum of 3 patients will be treated at each dose level prior to escalating to the next dose level. The decision to escalate to the next dose level will be made after the last additional patient on the current dose level has been observed through the first 12 weeks, in order to assess/rule out any dose limiting toxicity (DLT).

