## **10.3. Dose Escalation**

The operating characteristics of the dose escalation portion of this trial design are shown in the table below, which provides the probability of escalation to the next higher dose for each underlying true DLT rate. For example, for a DLT that occurs in 10% of patients, there is a greater than 90% probability of escalating. Conversely, for a DLT that occurs with a rate of 70%, the probability of escalating is 3%. (It is assumed that dose escalation occurs with either 0/3 or 1/6 patients with DLT).

| **Probability of Escalating Dose** | | | | | | | | | |  |
| --- | --- | --- | --- | --- | --- | --- | --- | --- | --- | --- |
| True Underlying DLT Rate | 10% | 20% | 30% | 40% | 50% | 60% | 70% | 80% | 90% | |
| Probability of Escalating Dose | 0.91 | 0.71 | 0.49 | 0.31 | 0.17 | 0.08 | 0.03 | 0.009 | 0.001 | |

The probability of failing to observe toxicity (such as DLT) in a sample size of 3 or 6 patients given various true underlying toxicity rates is shown below. For example, with 6 patients, the probability of failing to observe toxicity occurring at least 40% of the time is less than 5%.

| **Probability of Failing to Observe Toxicity** | | | | | | | | | |  |
| --- | --- | --- | --- | --- | --- | --- | --- | --- | --- | --- |
| True Underlying Toxicity Rate | 10% | 20% | 30% | 40% | 50% | 60% | 70% | 80% | 90% | |
| Probability Failing to Observe Toxicity, N=3 | 0.73 | 0.51 | 0.34 | 0.22 | 0.13 | 0.064 | 0.027 | 0.008 | 0.001 | |
| Probability Failing to Observe Toxicity, N=6 | 0.53 | 0.26 | 0.12 | 0.047 | 0.016 | 0.004 | <0.001 | <0.001 | <0.001 | |

##

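### After one related life-threatening DLT in six patients, section 4.2 escalates above a dose that section 4.5 already bars as the MTD, and no rule covers what follows

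*Protocol*

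**What the plan says.** Five places in the Protocol bear on this.

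- **Section 4.5, Maximum Tolerated Dose**, sets two joint conditions on the MTD. It is the highest dose "at which no subject experiences a life-threatening adverse event and at which 0/6 or 1/6 patients (<33%) experiences a DLT" in the 12 weeks after dosing.
- **Section 4.2, Dose Escalation Rules**, counts DLTs only: "If 1/6 patients experiences a DLT in the first 12 weeks, escalate to the next dose level". Its stopping rule is "The dose escalation will end after DLT is observed in ≥2 out of 3-6 patients treated at any dose level", or six patients observed at 15 mg/kg. If two or more of three patients have a DLT, the preceding level is to be brought up to at least six.
- **Section 4.4** ties DLTs to the drug: "Dose-limiting toxicity (DLT) is defined as any of the following when considered related to CP-675,206 therapy". Its first item is "Any CTC Grade 4 treatment related toxicity of any duration".
- **Section 6.1.1** lets escalation proceed only "if adequate safety is demonstrated at the previous CP-675,206 dose level tested", without saying what that means.
- **Section 10.3** states the basis of its escalation table: "It is assumed that dose escalation occurs with either 0/3 or 1/6 patients with DLT".

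**The concern.** Sections 4.2 and 4.5 apply different tests to the same dose, and neither refers to the other. A related life-threatening Grade 4 event is one DLT under 4.4. If it is the only DLT in six patients, 4.2 says escalate, while 4.5 has already ruled the dose out as MTD. New patients are then treated above a level that the plan's own criterion rejects.

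The MTD is the primary objective and is meant to set the Phase 2 dose. The sequence after such an event should therefore be written down. As it stands, if the higher dose fails there is no stated route to the dose that would have to be recommended.

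**Working it through.** **1. The rules side by side, for a cohort with one related life-threatening DLT in six patients**

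| Question | Section | Answer |
|---|---|---|
| Is the event a DLT? | 4.4 | Yes, one |
| Does escalation continue? | 4.2 | Yes, at 1/6 |
| Can this dose be the MTD? | 4.5 | No |
| Does the 10.3 table allow for this? | 10.3 | No, it uses 0/3 or 1/6 only |

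In the standard sequence the second three patients are added only after 1/3, so the DLT falls among the first three. Section 4.2 thus adds three more patients at the barred dose and then moves up.

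**2. What follows**

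- If the next dose gives two or more DLTs in three, 4.2 points to the preceding level. That is the barred level, which already has six patients. The level below it may have only three, and no rule expands it.
- If the next dose gives two or more DLTs in six, 4.2 only says that escalation is discontinued.
- At 15 mg/kg, escalation ends after six patients. If one of them had a life-threatening DLT, no rule sends the trial back to 10 mg/kg.

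**3. Reproducing the table in 10.3**

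Let p be the true DLT rate.

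P(escalate) = (1−p)³ + 3p(1−p)² × (1−p)³ = (1−p)³ + 3p(1−p)⁵

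- p = 10%: 0.7290 + 0.1771 = 0.9061 (stated 0.91)
- p = 20%: 0.5120 + 0.1966 = 0.7086 (stated 0.71)
- p = 30%: 0.3430 + 0.1513 = 0.4943 (stated 0.49)

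The other six columns reproduce as well. The second term is the 1/6 branch. It makes up 0.1771/0.9061 = 20%, 0.1966/0.7086 = 28% and 0.1513/0.4943 = 31% of escalations.

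**4. How often the conflict arises in the 1/6 branch**

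Let f be the share of DLTs that are life-threatening. The Protocol gives no value, so f is an assumption shown as a range.

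P(conflict) = f × 3p(1−p)⁵

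P(escalate if such an event stops escalation) = (1−p)³ + (1−f) × 3p(1−p)⁵

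| p | f | P(conflict) | P(escalate), as written | P(escalate), with the stop |
|---|---|---|---|---|
| 10% | 10% | 0.018 | 0.906 | 0.888 |
| 10% | 25% | 0.044 | 0.906 | 0.862 |
| 10% | 50% | 0.089 | 0.906 | 0.818 |
| 20% | 10% | 0.020 | 0.709 | 0.689 |
| 20% | 25% | 0.049 | 0.709 | 0.659 |
| 20% | 50% | 0.098 | 0.709 | 0.610 |
| 30% | 10% | 0.015 | 0.494 | 0.479 |
| 30% | 25% | 0.038 | 0.494 | 0.456 |
| 30% | 50% | 0.076 | 0.494 | 0.419 |

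The low end of f looks more realistic. Section 4.4 also counts Grade 2 autoimmune events of critical organs as DLTs. In the 44-patient single-dose study (section 2.3.2.1) there were three Grade 4 events, and "In all cases, the cause for the CTC Grade 4 event was not the study drug". That study had no radiation, and its doses started at 0.01 mg/kg.

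**5. Unrelated events**

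Section 4.5 has no relatedness condition. Read literally, a life-threatening event unrelated to CP-675,206 bars the dose with no DLT at all, and 4.2 still escalates after 0/3. Let u be the per-patient rate of such events, again an assumption. The chance of at least one in n patients is 1 − (1−u)ⁿ.

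| u | n = 3 | n = 6 |
|---|---|---|
| 2% | 0.059 | 0.114 |
| 5% | 0.143 | 0.265 |
| 10% | 0.271 | 0.469 |

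**The case against.** The best defence is that 4.2 and 4.5 govern different decisions. One says whether to test a higher dose, the other which dose to name at the end. A stricter test for the final dose can be deliberate, and a higher dose with at most 1/6 DLTs and no life-threatening event could still qualify after an isolated event one level down. That is correct, so escalation in this case is not pointless. It does not supply the missing step if the higher dose fails.

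A reader might infer that the trial could be left with no possible MTD. The text does not support that. Section 4.5 takes the highest dose that qualifies, so a lower level remains open. Sections 4.1 and 10.2 want at least six patients at the MTD, and 4.2 allows patients to be added at any level. What is missing is a rule that directs this.

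There are other controls: the adequate-safety condition in 6.1.1, the full 12-week observation of each cohort, the hospital's safety monitoring board and the interim safety analysis after dose level 2. Each leaves room for judgment, but none states what to do here.

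On relatedness, a reader might infer that any unrelated event certainly bars a dose. Section 9 defines a life-threatening experience in terms of the drug or biologic, which makes the narrower reading of 4.5 natural, although 4.5 does not use that term. Broader wording also has a purpose. A life-threatening reaction attributed to radiation rather than to CP-675,206 is not a DLT under 4.4, and only 4.5 would catch it. Nor is there a risk of sites reading the clause differently, because the Protocol describes one treating hospital.

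Finally, the Protocol equates Grade 4 with life-threatening only for diarrhea (6.1.4.1). Not every Grade 4 DLT need trigger the clause.

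**Conclusion.** The point holds as a conflict between rules. After one related life-threatening DLT in six patients, 4.2 escalates above a dose that 4.5 excludes. If the higher dose fails, the expansion rule leads back to the excluded level. At 15 mg/kg no step down is stated. This follows from the text and needs no assumed figure.

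Its frequency does rest on an assumption. With 10% of DLTs life-threatening, about 1.5% to 2% of cohorts are affected at true DLT rates of 10% to 30%. The shares of 25% and 50% are illustrations, not estimates.

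The relatedness gap is the lesser part. On the literal wording it extends the mismatch to the 0/3 branch, but it is partly a matter of drafting that section 9 softens. The figures in 10.3 are arithmetically correct for the rule they describe. They simply do not allow for the life-threatening clause.

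**What to change.** - **Section 4.2:** add that a life-threatening event considered related to study treatment (CP-675,206 or its combination with radiation) within 12 weeks of CP-675,206 dosing stops escalation above that dose, and that the next lower level is expanded to at least six patients. This also covers 15 mg/kg. At 3 mg/kg, which has no lower level, enrolment pauses for safety board review.
- **Section 4.5:** use the same wording, so that a life-threatening reaction to the combination still counts and a clearly unrelated event does not.
- **Section 6.1.1:** refer to this rule at the adequate-safety condition.
- **Section 10.3:** note under the escalation table that its probabilities assume no life-threatening event and are upper bounds otherwise.

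The drafting cost is a few sentences. The statistical cost is a modest fall in the probability of escalating, so a tolerable dose is passed over somewhat more often. At a 20% DLT rate it goes from 0.71 to about 0.69 with a 10% life-threatening share, and to 0.61 with a 50% share. Combination reactions that are not DLTs under 4.4 would lower it a little further, by an amount the documents do not allow one to calculate.

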# 5. STUDY POPULATION

## **5.1. Inclusion criteria**

1. Inoperable locally recurrent or metastatic breast cancer not amenable to curative therapy.
2. ECOG PS 0-1.
3. Age >18 years.
4. Radiation therapy for palliation is medically indicated.
5. The patient does not have any contraindications to receiving the radiation therapy dose specified in this protocol.
6. There are no restrictions on previous lines of therapy. Prior chemotherapy is permitted but ≥4 weeks must have elapsed since the last dose.
7. Adequate organ function as defined by the following criteria:
8. Serum ALT 1.5 x upper limit of normal (ULN);
9. Total serum bilirubin  2xULN (patients with Gilbert’s Syndrome – direct serum bilirubin 2 x ULN);
10. Absolute neutrophil count (ANC)  1500/L;
11. Platelets 100,000/L;
12. Hemoglobin 11.0 g/dL for male or  10.0 g/dL for female;
13. Alkaline phosphatase  2 x ULN;
14. Serum LDH  2 x ULN;
15. Serum creatinine clearance  30ml/min;
16. Serum lipase/amylase  1.5 x ULN;
17. Serum magnesium within normal institutional limits;
18. TSH within normal institutional limits;
19. Patients must have an absolute baseline ejection fraction of  institutional LLN by a gated MUGA or echocardiogram.
20. Able to sign and understand the informed consent document.

## **Exclusion criteria**

1. Previous treatment with any anti-CTLA4 agent.
2. Patients with active diarrhea at baseline.
3. Patients who will receive radiation to pelvic lesions (these patients will be excluded in order to minimize the risk of colitis).
4. History of chronic inflammatory or autoimmune disorder including, but not limited to the following: Addison’s disease, multiple sclerosis, Graves disease, Hashimoto’s thyroiditis, rheumatoid arthritis, systemic lupus erythromatosis, hypophysitis, pituitary disorders, pemphigus vulgaris, systemic mastocytosis, dermatomyositis/polymyositis, Sjörgen’s syndrome, vasculitis/arteritis, Behcet’s syndrome and psoriasis that is current or active in the last 3 years. Active vitiligo or a history of vitiligo will not be a basis for exclusion.
5. Patients with history of insulin-dependent diabetes.
6. History in the last 5 years of inflammatory bowel disease, celiac disease, or other chronic gastrointestinal conditions associated with diarrhea or bleeding not associated with the disease under study, or current acute colitis of any origin.
7. History (within the previous year) of congestive heart failure, stroke, myocardial infarction or thromboembolic event.
8. Patients with known brain metastases. Patients with clinical evidence suggestive of new brain metastases prior to enrollment are excluded if brain metastases have not been ruled out via CT or MRI. Patients with previously diagnosed brain metastases are eligible if they have completed their CNS treatment and have recovered from the acute effects of radiation therapy or surgery prior to the start of trial medication, have discontinued corticosteroid treatment for these metastases for at least 4 weeks, and are neurologically stable.
9. Patients of reproductive potential, who are not using an effective contraception, or who are pregnant or breastfeeding or have a positive (urine or serum) pregnancy test at baseline.
10. Concurrent or planned concurrent treatment with an immunosuppressive dose of corticosteroids or other immunosuppressive medication (eg, methotrexate, rapamycin) for longer than 10 days within 4 weeks prior to enrollment or while on-trial.
11. Any serious, uncontrolled medical disorder or uncontrolled active infection, including HIV or known or active viral hepatitis that would impair the ability to receive trial treatment and affect the risk/benefit ratio for the patient, in the judgment of the treating investigator.
12. Asymptomatic hepatitis C-positive patients would require a negative viral amplification by RT-PCR.
13. Psychiatric illness or social challenges that would preclude trial participation and compliance.

## **5.3. Enrolment criteria**

Following full assessment and determination that a patient meets all eligibility criteria and has given written informed consent for trial participation, the Investigator or designee will enroll the patient. Patients will be assigned individual patient identification numbers.

No patient shall receive investigational therapy until the entire registration process has been completed.

# TRIAL TREATMENTS

All patients being considered for the trial and eligible for screening must sign an informed consent form prior to any trial-specific procedures. Following completion of the pretreatment assessments and confirmation of eligibility, patients may be registered.

## **Trial Period**

Patients will receive radiation therapy and CP-675,206 on an outpatient basis. Radiation therapy will be given in 5 daily fractions. The radiation treatment can begin on either a Monday or a Tuesday. Clinic visits, hematology and other safety laboratory tests will be performed according to Table 2. Additional assessments may be performed as necessary to evaluate specific adverse events until they resolve to baseline or CTC Grade ≤1. Additional clinic visits may be required at the discretion of the investigator.

### **6.1.1. Dose Levels**

The starting dose of CP-675,206 will be 3.0 mg/kg, a dose shown to be safe as a single agent in previous trials. Dose escalation will only proceed to the 6, 10 and 15 mg/kg dose levels if adequate safety is demonstrated at the previous CP-675,206 dose level tested.

A minimum of 3 patients will be treated at each dose level prior to escalating to the next dose level. The decision to escalate to the next dose level will be made after the last additional patient on the current dose level has been observed through the first 12 weeks, in order to assess/rule out any dose limiting toxicity (DLT).

**CP-675,206 and radiation therapy: planned dose levels**

| Planned dose level | Radiation therapy | CP-675,206 dose  (given on the third day of radiation) |
| --- | --- | --- |
| 1  (starting dose) |  | 3 mg/kg |
| 2 | 2000cGy  (external, local radiation in 5 daily fractions) | 6 mg/kg |
| 3 |  | 10 mg/kg |
| 4 |  | 15 mg/kg |

### **6.1.2. Patient Dose Modifications (CP-675,206)**

#### 6.1.2.1. CP-675,206 dose adjustments due to changes in body weight

To adjust for possible fluctuations in body weight over time, patients will be weighed just prior to dosing, and the dose of CP-675,206 (re)calculated.

### **6.1.3. Patient Dose Modifications (Radiation Therapy)**

If the patient exhibits excessive toxicities, the last treatment or two may be omitted. The dose per treatment is not normally modified.

### **6.1.4. Management of CP-675,206 Toxicity**

CP-675,206 is an immune modulator, so Investigators should be alert for the development of immune-mediated side effects.

The majority of the adverse events reported in early phase trials have been manageable and well tolerated. The most common treatment-emergent, treatment-related adverse event is diarrhea. Diarrhea typically developed 1 to 2 months after the first dose of CP-675,206 (range: 4-72 days).

Although CP-675,206 is a fully human monoclonal antibody, immunogenicity remains a possibility, and thus acute hypersensitivity reactions such as urticaria, pruritus, laryngeal edema, angioedema, bronchospasm, respiratory distress, nausea, vomiting, abdominal cramps and pain, acute back pain, fever, diarrhea, hypotension and fatal anaphylactic shock, as well as sub acute reactions, are also possible. Possible immune-mediated disorders observed involve the skin (vitiligo and cutaneous leukocytoclastic vasculitis), the thyroid gland (autoimmune thyroiditis), the liver (autoimmune hepatitis), the pituitary (hypophysitis) and bone marrow (immune thrombocytopenic purpura). Abnormal lab results that may be immune-mediated include elevations of serum lipase and amylase and liver function tests. There has been one report of treatment-related uveitis, which resolved within 48 hours after treatment with topical steroids. Across all studies, toxicities generally recovered within 12 weeks, allowing continuation of treatment.

If a patient has an adverse event that is thought to be potentially immune-mediated (other than vitiligo), the Investigator should send a blood sample for autoimmune antibody testing.

CP-675,206 is a monoclonal antibody of the IgG2 type, and it is expected that it would cross the placenta if administered to a pregnant woman and could be secreted in breast milk of a lactating woman. The effect of exposure of a fetus or newborn to CP-675,206 is unknown. Women of childbearing potential must agree to use contraception during this trial and for 12 months after the last dose of CP-675,206.

*Note:* In general, it is not expected that the combination of CP-675,206 with this radiation dose will increase CP-675,206-related toxicities. However, radiation of the sites that are the most common autoimmune targets following CP-675,206 administration will be avoided when possible.

